## **6. Secondary efficacy outcomes analysis**

## **6.1 Definitions**

Secondary outcomes include all-cause hospital admissions and all-cause emergency department visits as separate outcomes, all-cause 30-day hospital readmissions, 30-day ED revisit rates, and connection to resources (visits to food pantry, receipt of utility shutoff protection letter).

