#### 4.2.2 Secondary Outcome Measures

Secondary outcomes measures will be measured by:

1. Total number of all-cause ED visits;
2. Total number of all-cause 30-day ED revisits;
3. All-cause 30-day ED revisits rate;
4. Total number of all-cause discharges from IP;
5. Total number of all-cause 30-day IP readmissions;
6. All-cause 30-day IP readmission rate.

Intermediate measures will be measured by:

1. Number and proportion of patients to have identified HRSN;
2. Number and proportion of patients to receive referrals for their HRSN;
3. Number and proportion of patients to receive community-based services to meet their HRSN;
4. Connection to housing resources;
5. Connection to employment resources;
6. Connection to food;
7. Patient-level average of Proportion of Days Covered (PDC) for pharmaceutical prescriptions.

A budget impact analysis will be conducted to estimate the short-term expenditure changes and financial consequences of THRIVE+ compared to THRIVE-Basic, focusing on direct costs of implementation (staffing, resources, eligible intervention population size, etc.).

Post-hoc measures:

1. Social determinants of health services or referrals (e.g., food pantry referrals, food pantry visits, utilities shut-off protection letters).

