### **12.3 Statistical Methods**

*Study consort diagram.*

*Data Analysis Plan.* Our primary outcome is the percentage change in all-cause hospital admissions and all-cause emergency department visits (a composite outcome) in the 12 months following enrollment. Secondary outcomes include total number of all-cause ED visits; all-cause 30-day ED revisits rate; total number of all-cause discharges from IP; all-cause 30-day IP readmission rate. Intermediate measures will be measured by: number and proportion of patients to have identified HRSN; number and proportion of patients to receive referrals for their HRSN; number and proportion of patients to receive community-based services to meet their HRSN; connection to housing resources; connection to employment resources; connection to food; and patient-level average of Proportion of Days Covered (PDC) for pharmaceutical prescriptions.

We will also collect data on demographics (age, gender, race, ethnicity, and language), insurance coverage (proportion of days covered from claims data), and on potential confounding variables, such as medical comorbidity as measured by the Elixhauser score), mental health and substance use diagnoses, THRIVE screening results, and medication adherence over 12 months using a measure of proportion of days covered based on pharmacy claims data.

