| Duration of follow-up | 12 months                                                                                                                                                                                                                                                                                                                                                                                                                                                                                                                                                                                                                                                                                                                                                                                                                                                                                                                                                                                                                                                                                                     |
| Criteria for efficacy | 
Measures:
We collect data on demographics (age, gender, race, ethnicity, and language), insurance coverage (proportion of days covered from claims data), and on potential confounding variables, such as medical comorbidity as measured by a validated comorbidity index (the Charlson Comorbidity Score), mental health and substance use diagnoses, health-related social needs screening results, and medication adherence using a measure of proportion of days covered based on pharmacy claims data.
 
Primary end points:
Our primary outcome is the percentage change in all-cause hospital admissions and all-cause emergency department visits (a composite outcome) in the 12 months following enrollment.
 
Secondary end points:
Secondary outcomes include all-cause hospital admissions and all-cause emergency department visits as separate outcomes, all-cause 30-day hospital readmissions, 30-day ED revisit rates, and connection to resources (referral to food pantry, visits to food pantry, utility shutoff protection letters).
 |

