|--|---------------------------------------------------------------------------------------------------------------------------------------------------------------------------------------------------------------------------------------------------------------------------------------------------------------------------------------------------------------------------------------------------------------------------------------------------------------------------------------------------------------------------------------------------------------------------------------------------------------------------------------------------------------------------------------------------------------------------------------------------------------------------------------------------------------------------------------------------------------------------------------------------------------------------------------------------------------------------------------------------------------------------------------------------------------------------------------------------------------------------------------------------------------------------------------------------------------------------------------------------------------------------------------------------------------------------------------------------------------------------------------------------------------------------------------------------------------------------------------------------------------------------------------------------------------------------------------------------------------------------------------------------------------------------------------------------------------------------------------------------------------------------------------------------------------------------------------------------------------------------------------------------------------------------------------------------------------------------------------------------|

- 11
- 12 **2. Major amendments to the protocol**
- 13 None
- 14
- 15 **3. Analysis population**
- 16 **3.1 Flow diagram**

Please see manuscript Figure.

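### The SAP names no outcome analysis for four of the protocol's seven intermediate measures (identified HRSN, housing, employment, PDC), narrows a fifth, discloses neither this nor the promotion of post-hoc measures, and leaves PDC as a possible post-enrolment covariate

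*Combined protocol and SAP*

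**What the plan says.** Protocol 4.2.2 lists seven intermediate measures. The first three are "Number and proportion of patients to have identified HRSN", "Number and proportion of patients to receive referrals for their HRSN" and "Number and proportion of patients to receive community-based services to meet their HRSN". Connection to housing, employment and food follow, and the seventh is "Patient-level average of Proportion of Days Covered (PDC) for pharmaceutical prescriptions". Protocol 12.3 repeats the list, beginning "Intermediate measures will be measured by: number and proportion of patients to have identified HRSN". Table 1 gives each measure a data source and a quarterly schedule covering all enrolled patients. Pantry referrals, pantry visits and utility protection letters stand apart, as post-hoc measures (4.2.2 and Table 2).

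The SAP names outcomes in three places: the synopsis row on criteria for efficacy, the synopsis row on statistical method, and section 6.1. Section 6.1 closes with "30-day ED revisit rates, and connection to resources (visits to food pantry, receipt of utility shutoff protection letter". The efficacy row adds pantry referral. The method row adds contact with, and services from, the community partner, in a list introduced as examples.

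In the SAP, adherence appears among the potential confounders, as "medication adherence using a measure of proportion of days covered based on pharmacy claims data", alongside social-needs screening results. SAP section 2, "Major amendments to the protocol", reads None. The synopsis, 5.1 and 5.3.2 all say that adjusted models will control for any factor found to differ significantly between the arms.

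**The concern.** The protocol commits to seven measures of how THRIVE+ is meant to work. The SAP carries forward some, changes others, and raises post-hoc measures to secondary status without saying so. A reader of the results could not tell which process outcomes were planned.

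Two consequences follow. First, Objective 3 concerns identifying and addressing social needs, and the SAP has no outcome analysis for identification. If utilization does not differ, the housing, employment and adherence measures are also among those that would help explain why. Second, moving PDC from outcome to covariate is not neutral. Medication adherence is what the pharmacy service in both arms sets out to improve, so adherence after enrolment can be affected by assignment. Adjusting for it could take out part of the effect that the primary analysis is meant to estimate.

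**Working it through.** **1. Are both texts current?** The protocol is Version 1.3, dated August 2021. SAP 3.2 has recruitment ending in March 2020, so 12-month follow-up ended about March 2021. The protocol still listed all seven measures after that, so this is not a comparison with superseded text.

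**2. Matching the measures.** A dash means not named as an outcome.

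| Protocol 4.2.2 measure | SAP synopsis, efficacy row | SAP synopsis, method row | SAP 6.1 | Result |
|---|---|---|---|---|
| 1 Identified HRSN | – | – | – | none |
| 2 Referrals | pantry | pantry; services via partner referral | – | narrowed |
| 3 Community services | – | partner contact and services | – | kept in one list |
| 4 Housing | – | – | – | none |
| 5 Employment | – | – | – | none |
| 6 Food | pantry | pantry | pantry visits | kept in some form |
| 7 PDC | – | – | – | none |

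Whole SAP: 4 with no outcome analysis + 1 narrowed + 2 kept in some form = 7. In section 6.1 alone, only food remains, so 7 − 1 = 6 are absent. The food match is loose: Table 1 takes food connection from community-partner data, whereas the pantry items are the warehouse-based post-hoc measures of Table 2.

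**3. The covariate route.** Protocol 12.3 lists adherence over 12 months as a potential confounder, without saying whether those months precede or follow enrolment. The SAP gives no window. Its adjustment rule covers any factor that differs significantly between arms and is not expressly limited to pre-enrolment factors. Taken together, these allow post-enrolment PDC, and likewise post-enrolment screening results, into the primary model.

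**4. Could PDC be analysed as an outcome?** The plan gives no PDC standard deviation or target difference, so there is no stated figure to reproduce. Inputs: 182 per arm (protocol 12.2, SAP 3.3); 80% retention (protocol 12.2), so 0.80 × 182 = 145.6, about 145 per arm; assumed SD 0.25 to 0.30; two-sided 0.05 and 80% power, so the multiplier is 1.96 + 0.84 = 2.80.

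Detectable difference = 2.80 × SD × √(2/n)

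- n = 182: √(2/182) = 0.1048. SD 0.25 gives 0.073; SD 0.30 gives 0.088.
- n = 145: √(2/145) = 0.1174. SD 0.25 gives 0.082; SD 0.30 gives 0.099.

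That is about 7 to 9 percentage points with everyone followed, and 8 to 10 at the planned retention, with no credit for baseline adjustment.

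**5. Where would the data come from?** Table 1 takes PDC from claims, and identified HRSN and referrals from the clinical data warehouse; these cover both arms. Services, housing, employment and food come from the community partner. On these the protocol conflicts with itself: the research follow-up text in section 9 has the partner check intervention-arm participants, while Table 1 says all enrolled patients.

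**The case against.** The strongest reply is that little has been lost. Protocol 12.3 lists the seven measures but gives none a model of its own, so the SAP removes no specified between-arm test. SAP 6.1 covers secondary outcomes, and silence about a separate intermediate tier need not cancel it. The method row's list is open-ended for social-need outcomes and could take in housing and employment. SAP 5.3.2 promises descriptive summaries of every variable, and PDC and screening results are still collected. The adjustment rule in SAP 5.1 follows a comparison of baseline characteristics, so baseline factors may be all that is meant.

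Much of this limits the point without removing it. An open list of social-need outcomes does not reach PDC, a descriptive summary is not an effect estimate, and an adjustment rule that may mean baseline factors should say so. The SAP does name some process outcomes and promotes post-hoc ones, so its silence on the others cannot be read as simply retaining them.

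Several stronger readings are tempting but unsupported:

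- **Five measures dropped.** Referrals are narrowed, not dropped.
- **The measures would go unreported.** They may be described; what is missing is a planned comparison.
- **Outcomes were chosen on their results.** The SAP quotes 136 of 364 patients with no visits, but that pools both arms and concerns utilization. The by-arm figures in SAP 4.2 are presented as characteristics at inclusion. Neither shows results for the omitted measures.
- **THRIVE+ will reduce adherence.** Protocol section 9 gives both arms the same pharmacy services, and the SAP synopsis gives the enhanced arm more time per patient. Nor does the hypothesis in protocol 12.1 mention medication adherence; it speaks of preventive care plans.
- **The None in SAP section 2 is false.** That section concerns protocol amendments, and the None in 5.2 concerns the primary outcome. Neither addresses intermediate measures.
- **PDC's double role began in the SAP.** The protocol already listed it both as an outcome and as a confounder; the SAP kept only the second role.

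**Conclusion.** The point holds in this form. Four of seven protocol intermediate measures have no SAP outcome analysis, one is narrowed, and measures the protocol calls post-hoc have become secondary outcomes, all without disclosure. No between-arm estimate is planned for PDC or for the identification part of Objective 3. That is an undisclosed change of outcomes, not just missing detail.

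The threat to the primary model is conditional. It arises if the adherence window runs after enrolment, PDC differs significantly between arms, and the adjustment rule is applied literally. The documents rule out none of these.

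The count rests on reading all three SAP lists together. The detectable PDC difference rests on an assumed SD; it shows that a comparison would be informative, not that a difference is expected.

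**What to change.** - **Tier and disclosure.** In SAP 6.1, restore the seven measures as a pre-specified intermediate tier. Add a list of every outcome dropped, narrowed or added relative to protocol 4.2.2, with the pantry and utility items shown as post-hoc in the protocol. Bring the three SAP outcome lists into line.
- **PDC.** Compare 12-month PDC between assigned arms by linear regression on claims data. Adjust for pre-enrolment PDC if it can be extracted; the documents do not say that it is collected.
- **Covariates.** Exclude post-enrolment PDC and post-enrolment screening results from every adjusted model.
- **Identified HRSN and referrals.** Compare arms from warehouse data. State that THRIVE+ navigators re-screen every three months while control liaisons do not screen systematically, so any difference partly reflects screening frequency.
- **Services, housing, employment and partner-sourced food connection.** First reconcile the section 9 text with Table 1. Compare arms only if control-arm data exist; otherwise report the THRIVE+ arm descriptively and say why.

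The cost is SAP wording, a few extra models and a longer results table. The claims and warehouse measures use sources already in the plan; the partner-sourced measures depend on what the partner supplied for control patients.

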## **6.2 Methods for analysis**

We will use similar methodology above to examine bivariate comparison and conduct adjusted analyses to examine the secondary outcomes.

## **7. Safety analysis**

N/A, this study involved no more than minimal risk to subjects.
